**Methods:**

BioBone is a prospective, blinded, multicenter biomarker validation study designed to assess the prognostic value of circulating CD8 + TEMRA cells in fracture healing. A total of 640 patients aged 18 to 80 years with fractures of the humeral diaphysis, radial and/or ulnar diaphysis, femoral neck, trochanteric femur, femoral diaphysis, distal femur, proximal tibia, tibial diaphysis and distal tibia will be enrolled. The study is powered to validate the target assay performance and accounting for 6–7 potential confounders at an expected incidence of 10% impaired healing. Biomarker levels will be measured pre- and post-operatively using flow cytometry (FC) and patients will be monitored for one year. The primary endpoint is fracture healing status at 17–19 weeks (normal healing or delayed healing), while the secondary endpoint evaluates healing at nine months (delayed healing or pseudarthrosis). Fracture consolidation will be assessed through radiographs or computed tomography (CT) scans in conjunction with clinical assessments such as range of motion and weight-bearing capacity. Key outcome measures include radiographic analysis (RUST/RUSH scores), functional and patient-reported outcomes (e.g. weight bearing ability, range of motion, and the SF-36 questionnaire), as well as socioeconomic parameters (e.g. work capacity, rehabilitation needs, mobility). The predictive performance (sensitivity, specificity, NPV, PPV) of the biomarker will be determined in a prospective, double-blinded analysis, where CD8 + TEMRA blood levels are measured prior to surgical treatment and healing status at clinical endpoints is assessed by independent observers. Additional immunological examination and in vitro analysis of blood and fracture hematoma samples will further investigate the mechanism of action of CD8 + TEMRA cells in impaired human bone regeneration.

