### Aims and Objectives

The aim is to conduct a prospective, blinded clinical validation study of the CD8 + TEMRA cells as a prognostic biomarker to predict healing outcome after fracture. Aimed test characteristics are a positive predictive value (PPV) > 60% and a specificity > 90%, as well as the clinical routine suitability or cost-effectiveness. We hypothesize that:

The perioperative cut-off level of CD8 + TEMRA cells (> 38%) is a prognostic marker with a high diagnostic accuracy to distinguish between patients with normal-, delayed or incomplete (non-union) fracture healing.Poor bone fracture healing can be predicted with a very high specificity (> 90%) prior to surgical intervention, allowing a more personalized treatment to improve the outcome with high cost effectiveness.As the biomarker reflects the pathogenic impact of TEMRA cells on fracture healing, precise identification of poor healers would offer novel immune-modulatory approaches to improve poor healing.

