#### Sample size calculation

A total number of 640 patients must be completely analyzed. This number is required to simultaneously construct a 97.5%-confidence interval with half-length of 3% for an expected specificity of 90% and a 97.5%-confidence interval with a half-length of 10% for an expected sensitivity of 85% associated with the assumed cut-off and a prevalence of delayed fracture healing of approximately 10%. The 97.5%-confidence intervals are used to maintain a global alpha error of 5%. Assuming a consent rate of 70% among patients meeting all inclusion and exclusion criteria and a dropout rate of 20%, approximately 1,140 patients will need to be screened to enroll 800 participants and obtain 640 complete datasets for analysis. Sample size calculation was done as described by Krummenauer and Kauczor [29]. According to this sample size, we use Harrell's rule that 10 to 20 events per independent predictor variable are necessary to ensure a stable regression model. With the above sample size, approximately 6 predictor variables, respective covariables or confounders 640*0.1/10 can be entered in a final logistic regression model to discriminate regarding the fracture healing outcome [30].

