**Post surgery information (FU visits V4 – V8)**	
Chronic, non-fracture related medication	See “chronic diseases and medication”
Post surgery, fracture related, medication	Usage and duration of vitamin K antagonists, Factor Xa and thrombin inhibitors, acetylsalicylic acid, steroidal anti-inflammatory drugs, non-steroidal anti-inflammatory drugs (NSAID), opioid analgesics
Healing evaluation	X-ray and/or computed tomography, bone consolidated (yes/no), radiographic union scale in tibial fractures (RUST score), radiographic union score for hip (RUSH score), implant set (no/yes; knee joint replacement, hip joint replacement), patient weight-bearing capacity (No load, partial load < 2 kg, 5—10 kg, 10—15 kg, 20 kg, 30 kg, full weight bearing)
X-ray and/or CT images	Storage of the images in eCRF data base
Health economics	Time point of ability to work, payment of sickness benefit, duration and length of physiotherapy units, use of walking aids (armpit supports, walking frame, crutches, rollator), duration of inpatient/partial inpatient stay in a rehabilitation clinic
Patient Reported Outcome Measures	SF-36
Infection status	Pathogen spectrum, medical and/or surgical treatment
Fracture revision treatments	Type and numbers of additive surgical treatment procedures (dynamization, change of procedure within osteosynthesis or to endoprosthesis, use of adjuvants) type and numbers of additive non-surgical fracture treatment procedures (e.g. extended outpatient physiotherapy (EAP), shockwave therapy)

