#### Statistical analyses

An optimal cut-off value for circulating CD8 + TEMRA cell levels (> 38%) was determined in a retrospective pilot study [23]. This predefined threshold, alongside an optimized cut-off identified within the multivariable prediction model, will be used to predict the healing outcome of patients. Based on the final clinical healing classification, sensitivity, specificity and other diagnostic accuracy measures will be calculated for CD8 + TEMRA levels within the covariate-adjusted model. CD8 + TEMRA cells level, together with auxiliary covariates and selected confounders, will be entered into a logistic regression model to predict the occurrence of delayed fracture and non-fracture healing beyond the biomarker alone and/or adjusted. Putative key covariates and confounders are age, sex, diabetes type II, NSAID use, rheumatoid arthritis and osteoporosis. Variable selection will be done using the AIC and validated by using bootstrapping methods. The diagnostic ability of the resulting prediction score will be measured using e.g. Nagelkerkes R2N, Somers Dxy, Brier Score and misclassification error. Further, the score will be analyzed by using AUC/ROC curve and the Youden index. Sensitivity, specificity, NPV, PPV, positive LR and negative LR including 95%-confidence intervals will be calculated. Calibration will be evaluated via calibration plot and goodness-of-fit will be tested using Hosmer–Lemeshow-Test and pseudo-R^2^ measures [30].

For missing data, the proportion of missingness will be assessed. If more than 5% of values are missing, multiple imputation (MI) by chained equations (MICE) will be applied under the assumption that data are Missing Completely at Random (MCAR) or Missing at Random (MAR). The imputation model will include all covariates, outcome variables, and relevant auxiliary variables that may inform the missingness mechanism. A minimum of 20 imputations will be generated. To assess the robustness of the results, sensitivity analyses will be conducted by comparing the multiply imputed datasets with complete-case analyses. Additional variables will be analyzed using appropriate parametric or non-parametric statistical tests, depending on scale and distribution. All p-values from secondary analyses will be interpreted in an exploratory, non-confirmatory manner. All statistical analyses will be done using SAS (version 9.4) and R (latest version at time of analysis).

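### NSAID use enters the prediction model without a time window, and the only general NSAID item is recorded after surgery, so the resulting score may not be usable before surgery

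*Protocol article*

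**What the plan says.** **Purpose.** Under Aims and Objectives, the second hypothesis is that poor healing "can be predicted with a very high specificity (> 90%) prior to surgical intervention". The abstract likewise sets its performance target for identification before the operation: at least 30% of impaired healers, at a specificity above 90%.

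**Model.** Under Statistical analyses, "CD8 + TEMRA cells level, together with auxiliary covariates and selected confounders, will be entered into a logistic regression model". The named variables are: "Putative key covariates and confounders are age, sex, diabetes type II, NSAID use, rheumatoid arthritis and osteoporosis". The same section takes an optimised cut-off from this model, reports accuracy for the biomarker within the covariate-adjusted model, and assesses the score by ROC curve and Youden index. On selection: "Variable selection will be done using the AIC and validated by using bootstrapping methods".

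**Data.** Table 2 has NSAIDs in two places. The post-surgery block (V4 to V8) covers use and duration of fracture-related medication, including "steroidal anti-inflammatory drugs, non-steroidal anti-inflammatory drugs (NSAID), opioid analgesics". The chronic disease block (visits 1 to 8) lists NSAIDs only among treatments of rheumatoid disease. Table 3 places the primary endpoint at V6, week 17 to 19.

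**Number of predictors.** The sample size section says that "approximately 6 predictor variables, respective covariables or confounders 640*0.1/10 can be entered in a final logistic regression model", from a rule that "10 to 20 events per independent predictor variable are necessary to ensure a stable regression model". The abstract speaks of "accounting for 6–7 potential confounders at an expected incidence of 10% impaired healing".

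**The concern.** A pre-operative prediction model can use only what is known before the operation. For patients without rheumatoid disease, the data listed in Table 2 can supply NSAID use only from post-surgery records, and part of that record is made at or after the visit where the outcome is judged. Two things follow if the covariate is built from that item.

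- The score cannot be computed at the time when it is meant to guide treatment.
- Patients whose fracture is slow to heal may take NSAIDs because of it. The outcome would then feed back into a predictor, and the score would look more accurate than any score available before surgery.

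This bears on main results, because the reported covariate-adjusted sensitivity and specificity and the optimised cut-off come from the same model. With an abstract target of 30% sensitivity, a gain of a few points that no surgeon could obtain in practice might decide whether the covariate-adjusted result appears to meet it.

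**Working it through.** **1. Timing, item by item**

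| Element | Where in the protocol article | Timing |
|---|---|---|
| Intended prediction | Aims and Objectives; abstract | before surgery |
| NSAID use as covariate | Statistical analyses | not stated |
| NSAIDs, fracture-related | Table 2, post-surgery block | V4 to V8 |
| NSAIDs for rheumatoid disease | Table 2, chronic diseases block | visits 1 to 8 |
| Primary endpoint | Table 3 | V6 |

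The general item lies wholly after surgery, and V7 and V8 lie after the primary endpoint. The one earlier item applies to rheumatoid disease only, so it cannot describe NSAID use in the whole cohort.

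**2. How much a non-causal NSAID covariate could add (illustration)**

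From the abstract: 30% sensitivity at 90% specificity. Assumptions, not in the documents:
- the biomarker is normal with equal variance in both groups;
- NSAID use has no effect on healing and is independent of the biomarker within each outcome group;
- 30% of normal healers are recorded users, and the share q among delayed healers varies.

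The separation of the biomarker is d = z(0.30) + z(0.90) = −0.524 + 1.282 = 0.757. Alone it gives AUC = Φ(0.757/√2) = 0.704.

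The logistic score is d·x + b·N, where x is the standardised biomarker, N is NSAID use (0 or 1) and b = logit(q) − logit(0.30). The threshold is set so that overall specificity is 90%.

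Worked case, q = 50%: b = 0 − (−0.847) = 0.847. The biomarker thresholds become 1.797 for non-users and 0.678 for users, which differ by b/d = 0.847/0.757 = 1.119.
- False-positive rate: 0.70·Φ(−1.797) + 0.30·Φ(−0.678) = 10.0%.
- Sensitivity: 0.50·Φ(0.757 − 1.797) + 0.50·Φ(0.757 − 0.678) = 34.0%.

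| Users, delayed vs normal | AUC | Sensitivity at 90% specificity | Gain |
|---|---|---|---|
| 30% vs 30% | 0.704 | 30.0% | 0 |
| 40% vs 30% | 0.711 | 31.1% | 1.1 points |
| 50% vs 30% | 0.729 | 34.0% | 4.0 points |
| 60% vs 30% | 0.757 | 38.6% | 8.6 points |

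The base matters. The sample size section expects 85% sensitivity instead, so d = 1.036 + 1.282 = 2.318. The same three rates then give 85.2%, 85.8% and 86.8%, gains of 0.2 to 1.8 points.

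**3. Predictor count (separate)**

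The plan's figures reproduce. For sensitivity with a two-sided 97.5% interval, n = 2.2414² × 0.85 × 0.15 / 0.10² = 64.05 events, and 64.05/0.10 = 640.5, which matches 640. The predictor limit is 640 × 0.1 / 10 = 6.4, hence about 6.

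- Named candidates: biomarker + 6 covariates = 7, and 64/7 = 9.1 events each.
- Abstract, upper count: 7 confounders + biomarker = 8, and 64/8 = 8.0.
- Without any one of the six covariates: 64/6 = 10.7.

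**The case against.** **The window is not stated.** A reader might infer that the model does leak outcome information. The document does not say so: it names NSAID use without saying which visits count. Baseline use may be meant, and because use and duration are recorded, a window closing before V6 may be definable. An exact covariate definition is often left to an analysis plan that is not shown here. This stands, so leakage is permitted rather than certain. It does not remove the point, because the article itself fixes the covariate list, the data items and the pre-operative claim. If baseline use is meant, Table 2 shows no general item to supply it. If a window between surgery and V6 is meant, the score still cannot be used before surgery.

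**Adjustment is a legitimate role.** The section speaks of confounders as well as covariates, and post-operative exposure may be examined to see whether the biomarker association persists. That is fair for an explanatory analysis, but the same model also yields the score, the cut-off and the reported accuracy.

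**The biomarker alone is safe.** Correct: the predefined >38% threshold applied to the biomarker alone does not depend on how NSAID use is coded.

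**Bootstrap validation is planned.** It addresses instability from selection. It does not address leakage, since each resample carries the same post-operative information.

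**The user rates are assumed.** Correct: they have no source in the documents, and equal use gives no gain. The calculation shows what a difference would do, not that one exists.

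**NSAID use and the predictor limit.** It is tempting to say that NSAID use breaks the plan's own cap. It does not: dropping any one covariate has the same effect, and the limit is approximate and refers to the final model after AIC selection. Counting candidates is the sounder reading, because selecting on the data does not remove its overfitting cost, but it is not how the plan words its limit.

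**Conclusion.** The point holds as a mismatch between the covariate list, the data schedule and the stated use of the model. Built from the listed general item, the score would need information that does not exist before surgery and that may reflect healing itself. Its accuracy, optimised cut-off and covariate-adjusted sensitivity and specificity could then look better than any usable pre-operative score.

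The size is uncertain. It is about 1 to 9 points of sensitivity at 90% specificity if 40% to 60% of delayed and 30% of normal healers are users and the biomarker performs at the abstract's target. It is under 2 points at the 85% sensitivity assumed for the sample size, and nil if use is equal. The documents do not support saying that leakage will occur, or that the result for the biomarker alone is compromised.

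The predictor count is a minor inconsistency: 7 named candidates at 9.1 events each, against about 6 in the sample size section and 6 to 7 confounders in the abstract.

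**What to change.** 1. State that the pre-operative prediction model, its optimised cut-off and all accuracy measures reported from it use only values known before surgery. Leave post-operative NSAID use out of that model.
2. If post-operative NSAID exposure is of interest, analyse it in a separate model labelled explanatory, counting only exposure before V6.
3. Reconcile the number of predictors across the abstract, the sample size section and the analysis section, and say whether the biomarker is included in the count. With step 1, the named candidates fall to six (64/6 = 10.7 events each), within the plan's rule at 10 events per predictor.

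The cost is a change of wording before unblinding. One covariate is lost from the score, and apparent performance may be slightly lower. No change to recruitment or sample size is needed.

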**Life Style (FU visits 1–3)**	
Smoking status	Smoker, previous smoker, non-smoker
Alcohol consumption	Units/week
Sporting activities	Activity type, h/week,

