**Surgery and fracture related information (FU visits 1–3)**	
Number of fractures	1 or ≤ 2
ASA score	I—IV
AO classification	Femur, tibia, humerus, forearm
Degree of soft tissue damage	0—3
Primary surgery (if applicable)	Date, duration, type of fixation (e.g. cast, external fixator)
Final surgery	Date, duration, type of surgery (external fixator, angular stable plate, LISS plate, screw osteosynthesis, intramedullary nail osteosynthesis, compression plate, neutralization plate, others), usage of adjuvants (BMP-2, platelet rich plasma, autologous cancellous bone graft, allogeneic cancellous bone graft, local application of antibiotics, local muscle flap, remote muscle flap, others)
Blood collection	Date and time of pre- and post-surgery blood collection

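### NSAID use is named as a covariate of a pre-operative score but is generally recorded only after surgery and past the primary endpoint; a coarse fracture-region term should be pre-specified

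*Protocol article*

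**What the plan says.** The Statistical analyses section of the protocol article describes the model in these words: "CD8 + TEMRA cells level, together with auxiliary covariates and selected confounders, will be entered into a logistic regression model". It then gives the candidates: "Putative key covariates and confounders are age, sex, diabetes type II, NSAID use, rheumatoid arthritis and osteoporosis". On selection it says: "Variable selection will be done using the AIC and validated by using bootstrapping methods". Sensitivity, specificity and the other accuracy measures are to be calculated for the biomarker within this adjusted model. The fixed >38% threshold from the pilot study is used alongside an optimised cut-off from the model.

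Both the Abstract and Aims and Objectives place the prediction before surgery.

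Table 2 shows when each variable is recorded:

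- NSAIDs in general are in the row "Post surgery, fracture related, medication", as use and duration, under the block for visits V4 to V8.
- NSAIDs appear once more among chronic diseases and medication (visits 1–8), but only as a therapy for rheumatoid disease.
- Fracture site is in the AO classification row ("Femur, tibia, humerus, forearm"), in the block headed "Surgery and fracture related information (FU visits 1–3)".
- Smoking status ("Smoker, previous smoker, non-smoker") is in the Life Style block, also visits 1–3.

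The Sample size calculation section allows "approximately 6 predictor variables, respective covariables or confounders" in the final model.

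**The concern.** A prognostic score can use only what is known when the prediction is made. Here that is before surgery. The one general NSAID field opens after surgery and continues to V8, while the primary endpoint is V6. A patient who heals slowly may take analgesics for longer, so use and duration could be a result of the outcome rather than a predictor of it. If that variable enters the score, the reported sensitivity, specificity and AUC describe a test that nobody could run at admission.

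The planned safeguards would not catch this. AIC tends to keep a variable that carries information about the outcome, whatever the reason. Bootstrap resampling reuses the same patients with the same post-operative values, so it corrects for overfitting but not for information that arrives too late.

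The second, smaller matter is fracture site. The Abstract pools nine locations, from forearm shaft to femoral neck, and Table 3 judges all of them in one window. The radiological scale also differs by site (RUST for the tibia, RUSH for the hip, with thresholds of >10 and >24). Site is recorded and known at admission, yet no site term is named.

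**Working it through.** **1. Timing of NSAID use**

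| Item | Timing | Source |
|---|---|---|
| Intended prediction | before surgery | Abstract; Aims and Objectives |
| General NSAID use and duration | V4–V8, after surgery | Table 2, Post surgery information |
| NSAIDs as rheumatoid therapy | visits 1–8 | Table 2, Chronic diseases and medication |
| Primary endpoint | V6, weeks 17–19 | Table 3 |
| Secondary healing endpoint | V7, weeks 34–36 | Table 3 |

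Entries at V4 and V5 precede the endpoint but are still post-operative. Entries at V7 and V8 follow it. The rheumatoid entry has early visits, but it covers only patients with rheumatoid disease and overlaps another named covariate. So no general pre-operative NSAID variable appears in Table 2. The documents give no NSAID frequency by healing status, so the resulting inflation of accuracy cannot be calculated.

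**2. Events budget**

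The plan's own figures reproduce. With z = 2.2414 for a two-sided 97.5% interval:

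- sensitivity: 2.2414² × 0.85 × 0.15 / 0.10² = 64.05 cases, and 64.05 / 0.10 = 640.5 patients
- specificity: 2.2414² × 0.90 × 0.10 / 0.03² = 502.4 non-cases, and 502.4 / 0.90 = 558.2 patients
- the larger gives the stated 640; events = 640 × 0.1 = 64; 64 / 10 = 6.4 predictors

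Events per term for the alternatives:

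| Model | Terms | Events per term |
|---|---|---|
| Biomarker + six named | 7 | 64 / 7 = 9.1 |
| NSAID removed | 6 | 64 / 6 = 10.7 |
| NSAID removed, one region contrast added | 7 | 64 / 7 = 9.1 |
| As above, plus smoking as one contrast | 8 | 64 / 8 = 8.0 |
| NSAID removed, site with four levels (3 df), smoking with three (2 df) | 11 | 64 / 11 = 5.8 |

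**3. How large could site confounding be?**

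These inputs are assumptions: two equal site groups, delayed healing of 5% and 15%, and no biomarker effect within either group. The Introduction gives 5–15% as an overall prevalence range, not as a contrast between sites.

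- Biomarker-high in 10% and 20%: risk if high = (0.5×0.10×0.05 + 0.5×0.20×0.15) / 0.15 = 0.117; risk if low = (0.5×0.90×0.05 + 0.5×0.80×0.15) / 0.85 = 0.097; odds ratio 1.23.
- Biomarker-high in 10% and 30%: risks 0.025 / 0.20 = 0.125 and 0.075 / 0.80 = 0.094; odds ratio 1.38.
- A second set of assumptions (10% overall risk, 30–50% of patients at the higher-risk site, site–outcome odds ratio 1.5–3) gives 1.04–1.13 for high shares of 15% and 22%, and 1.11–1.35 for 12% and 30%.
- Equal shares give 1.00.

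For comparison, the Abstract's 30% sensitivity with 90% specificity implies (0.30/0.70) / (0.10/0.90) = 3.9. The sample-size values of 85% and 90% imply (0.85/0.15) / (0.10/0.90) = 51.

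**4. Precision by region**

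Assume events spread evenly, and the planned 85% sensitivity. Two equal regions have 32 events each, with a 95% half-width of 1.96 × √(0.85×0.15/32) = 12 percentage points. Four equal regions have 16 each, with 17 points.

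**The case against.** The strongest reply is that the list is only putative. The model also admits unnamed auxiliary covariates and selected confounders, and a condensed article may leave the final candidates to the analysis plan. That stands for site and smoking: they are unnamed, not excluded. It does not rescue NSAID use, which is named as a key covariate with no time window, while the only general field collected for it is post-operative.

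It can also be said that NSAIDs are recorded from visit 1. That is true only for rheumatoid therapy.

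A reader might infer that the adjusted biomarker effect is confounded by site and smoking. The documents do not support that. No passage relates either variable to the CD8+ TEMRA level, and none gives healing rates by site or by smoking. The odds ratios above come from assumed inputs and are small beside the targets. Nor does the covariate list affect the pooled accuracy of the fixed >38% cut-off used alone; there the question is only whether accuracy differs by region.

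A reader might also think that exchanging NSAID use for both smoking and a region term costs nothing. It does not balance: one term leaves and two enter, so 7 terms become 8.

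**Conclusion.** The point holds for NSAID use. As recorded, it cannot belong to a pre-operative score, and part of it is collected after the primary endpoint. Any accuracy reported from a score that contains it would not be the accuracy of a pre-operative test. The size of the effect is unknown from the documents and depends on how use and duration differ by healing status, and on whether AIC retains the variable.

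For fracture site the conclusion is weaker. Pooling nine locations against one window, with the site already recorded, is sufficient reason to pre-specify a coarse term and to describe accuracy by region. It is not evidence of bias: confounding remains a possibility, with illustrative odds ratios of 1.23 to 1.38 under assumed inputs. Smoking is optional; a sentence justifying its inclusion or omission would do.

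**What to change.** In Statistical analyses:

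1. State that the pre-operative score uses only variables known before surgery. Remove NSAID use from it, or define it as documented pre-operative use. Put post-operative NSAID use in a separate explanatory or sensitivity analysis. For the conditions recorded at visits 1–8 (diabetes, rheumatoid disease, osteoporosis), say that the status before surgery is used.
2. Pre-specify one coarse fracture-region term, keep it in the model regardless of AIC, and use penalised estimation.
3. Tabulate sensitivity and specificity of the >38% cut-off by region, labelled as descriptive.

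Cost: for NSAID removal and the region term, a change of wording only, since site is already collected. Documented pre-operative NSAID use would need a source, because Table 2 shows no general field for it. With NSAID use removed and one region contrast added, the model keeps 7 terms and 9.1 events per term; adding smoking makes 8 terms and 8.0. Penalisation limits instability but does not add events. Regional estimates will be imprecise, and one named covariate leaves the pre-operative score. The change should be made before outcomes are analysed.

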## Abstract

**Aims:**

The BioBone consortium aims to validate circulating CD8 + TEMRA cells as a prognostic biomarker for predicting impaired fracture healing outcomes in a prospective, blinded, multicenter clinical study. The primary performance parameters are the pre-operative identification of at least 30% of patients who ultimately experience impaired healing at the first clinical endpoint, with a specificity greater than 90% to minimize the false-positive rate.

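### The optimised cut-off is not tied to the goal of specificity above 90%, and the one conventional ROC cut-off criterion named, the Youden index, can place it below that goal

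*Protocol article*

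**What the plan says.** The performance goals put specificity first. The abstract's Aims paragraph asks for "pre-operative identification of at least 30% of patients who ultimately experience impaired healing at the first clinical endpoint". It couples this target to a condition on the other error: "with a specificity greater than 90% to minimize the false-positive rate". The Aims and Objectives section sets "a positive predictive value (PPV) > 60% and a specificity > 90" per cent, and its second hypothesis reads "Poor bone fracture healing can be predicted with a very high specificity (> 90%) prior to surgical intervention".

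The Statistical analyses section names two prediction rules. One is the threshold of >38% from the retrospective pilot study. It is used "alongside an optimized cut-off identified within the multivariable prediction model". No rule for finding that second cut-off is given at that point. Later in the same paragraph, after a list of overall performance measures (Nagelkerke R², Somers' Dxy, Brier score, misclassification error), the article adds: "Further, the score will be analyzed by using AUC/ROC curve and the Youden index". Sensitivity, specificity, predictive values and likelihood ratios are then to be reported.

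The sample size section plans at a different operating point from the abstract: a "97.5%-confidence interval with half-length of 3% for an expected specificity of 90" per cent and a "97.5%-confidence interval with a half-length of 10% for an expected sensitivity of 85" per cent, at a prevalence of about 10%.

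**The concern.** The stated use is that of a rule-in test: few false positives, even if many impaired healers are missed. The Youden index maximises sensitivity + specificity − 1. It gives one point of sensitivity the same value as one point of specificity, has no specificity floor, and takes no account of the roughly 9:1 ratio of normal to impaired healers. When discrimination is moderate, its maximum usually lies well to the sensitive side of 90% specificity.

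If the optimised cut-off is placed this way, it may be reported at an operating point that fails the trial's specificity goal even though the same score could meet it. The false-positive rate and PPV shown for that cut-off would then describe a different test from the one the aims call for. Leaving the criterion open also allows a choice, once results are known, between a cut-off that looks sensitive and one that looks specific.

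**Working it through.** **Inputs from the article.** Analysed patients 640; prevalence about 10%, so 64 impaired and 576 normal healers; goal of sensitivity at least 30% with specificity above 90% (abstract); goal of PPV above 60% (Aims and Objectives); planning values of sensitivity 85% and specificity 90% (sample size section).

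**Assumption, not in the article.** The score is normally distributed in each outcome group. The SD ratio (impaired/normal healers) is 1 in the base case and is varied from 0.67 to 2.

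**Step 1: the plan's own figure.** With z = 2.2414 for a two-sided 97.5% interval, n = z²p(1−p)/h².
- Sensitivity: 2.2414² × 0.85 × 0.15 / 0.10² = 64.05 cases; divided by 0.10, 640.5 patients.
- Specificity: 2.2414² × 0.90 × 0.10 / 0.03² = 502.4 non-cases; divided by 0.90, 558.2 patients.

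The larger value reproduces the stated 640, so the counts of 64 and 576 match the plan.

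**Step 2: Youden point with equal SDs.** Fix the ROC curve to pass through the stated operating point: d = z(specificity) + z(sensitivity). The Youden maximum is where sensitivity = specificity = Φ(d/2), and AUC = Φ(d/√2).
- 30%/90%: d = 1.2816 − 0.5244 = 0.757; AUC 0.70; Youden point 64.7%/64.7%. Youden's J rises from 0.200 to 0.295. False positives go from 576 × 0.10 = 58 to 576 × 0.3525 = 203. PPV goes from 25% to 41.4/(41.4 + 203.0) = 17%.
- 70%/90%, an intermediate case: d = 1.2816 + 0.5244 = 1.806; Youden point 81.7%/81.7%; 106 false positives.
- 85%/90%: d = 1.2816 + 1.0364 = 2.318; AUC 0.95; Youden point 87.7%/87.7%; 71 false positives; PPV from 49% to 44%.

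With equal SDs, the Youden point reaches 90% specificity only if AUC is at least Φ(2 × 1.2816/√2) = 0.965.

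**Step 3: unequal SDs.** With normal healers at mean 0 and SD 1 and impaired healers at SD s, set the impaired mean to z(specificity) − s·z(1 − sensitivity) and maximise J numerically.

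| Marker (sens/spec) | s = 0.67 | s = 1 | s = 1.5 | s = 2 |
|---|---|---|---|---|
| 30%/90% | 61.7% | 64.7% | 82.9% | 90.2% |
| 70%/90% | 79.4% | 81.7% | 86.6% | 90.1% |
| 85%/90% | 85.3% | 87.7% | 91.0% | 93.3% |

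Entries are Youden specificity. For 30%/90% the lowest value in this range is 61.0%, near s = 0.77.

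**Step 4: what a specificity floor does for PPV.** At 10% prevalence, PPV = 0.1·sens / (0.1·sens + 0.9·(1 − spec)).
- At exactly 90% specificity and perfect sensitivity: 0.10/(0.10 + 0.09) = 53%.
- PPV of 60% with perfect sensitivity needs 1 − spec = 0.1 × (0.4/0.6)/0.9 = 0.074, so specificity of 92.6%.
- PPV of 60% with 30% sensitivity needs 1 − spec = 0.3 × 0.1 × (0.4/0.6)/0.9 = 0.022, so specificity of 97.8%.

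**The case against.** The strongest reply is textual. The article says the score is analysed by the Youden index, within a list of performance summaries. It does not say that the index selects the cut-off. A reader might infer that the plan commits to a Youden cut-off and that a marker meeting the goal would be moved to 65% specificity. The text does not support a statement that firm. Nor is Youden the only threshold-dependent measure listed: misclassification error also depends on the threshold and, at 10% prevalence, favours high specificity. Both points stand. Youden remains the only conventional ROC cut-off criterion named, which makes it the natural reading.

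It can also be said that a condensed article may leave the selection rule to the full protocol or SAP. That is fair, and a missing rule alone would be no finding. Here, however, the article makes the optimised cut-off one of its two prediction rules and names a criterion that does not match its own goal.

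The 65% figure is open to challenge. The 30% is a floor and not an expected value, the documents give no score distribution, and the discrimination of the multivariable score is unknown. At the planning values the equal-SD shortfall is only about 2 points, and at an SD ratio of 2 it disappears. A 30%/90% marker also has a PPV of 25%, so it does not meet the PPV goal. If specificity is instead set to 97.8% to reach a PPV of 60% at 30% sensitivity, the equal-SD Youden specificity is about 77%. All of this stands, so the figure is an illustration to be shown with its range.

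Finally, a reader might infer that the validation as a whole is compromised. It is not: the first hypothesis concerns >38%, the sample size is tied to an assumed cut-off, and no ROC criterion can move a fixed threshold.

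**Conclusion.** The concern holds for the optimised cut-off only. Nothing in the article ties that cut-off to specificity above 90%, and the criterion most readily taken to set it can place it below that goal. How far below depends on which of the article's own operating points applies and on the unknown score distribution: Youden specificity of about 65% (61% to 90%) for a 30%/90% marker, and about 88% (85% to 93%) for an 85%/90% marker, under assumed normality and SD ratios of 0.67 to 2. In the first case with equal SDs, false positives rise from 58 to 203 of 576. The change is worth making because it is cheap and protects the meaning of one of the two reported rules. It does not threaten the evaluation of the fixed threshold.

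**What to change.** In the Statistical analyses section (and in the SAP, if it is silent), define the optimised cut-off as the value that maximises sensitivity subject to specificity above 90%. Repeat the selection within each bootstrap sample, so that the optimism of choosing and evaluating the cut-off on the same patients is captured. Report sensitivity, specificity, PPV and NPV at that cut-off, and keep the Youden index as a descriptive summary only.

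Report PPV there against the >60% goal, and note that at 10% prevalence this goal needs specificity of at least about 92.6% even with perfect sensitivity. Meeting the 90% floor should therefore not be presented as meeting the PPV goal.

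The cost is a few sentences and a few lines of code, with no extra patients or data. The downside is that sensitivity at the optimised cut-off will look lower than at the Youden point wherever the floor binds. The rule should be fixed before biomarker and outcome data are linked.
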